### Strengths and limitations

Many methodological requirements for a high quality trial are met. Allocation is concealed through randomization by an external researcher. Recruitment of the patients will be done after the standard intake procedure at each site. As this study takes place within different general mental healthcare departments located in different parts of the Netherlands the results can, to a large extent, be generalized to the population of borderline patients seen in regular mental healthcare in the Netherlands. A limitation of the present study is that the assessments will be performed by research assistants who cannot remain blinded to the treatment condition of the included patients, as is always the case in trials studying the effects of psychotherapy. Nor are the patients blind to treatment condition. In this study, however, added to the main interview-based outcome measures, self-report questionnaires will be administered, that will not be influenced by the research assistants.

Another limitation is the power of this study. This implementation study is powered to demonstrate a medium or higher effect of TTA. The failure to detect any difference between conditions, does not mean that they are equivalent, only that differences, if any, will be small. A small difference however does not imply lack of clinical significance. But to detect a small effect with a significance level of .05 and a power of 80, a power analysis shows that a sample of more than 3100 patients is necessary, which is not feasible for a trial on long-lasting psychotherapy.

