In sum, this study will test the implementation of ST for BPD in regular mental healthcare and will compare two modalities: one with extra crisis support by the therapist outside office hours and one without such telephone support. The study has three aims. First, to assess whether patient outcomes after 1.5 years of ST will be the same when implemented in regular practice, compared to what was found in the RCT [1]. Since rigorous evaluations such as RCTs always imply controlled conditions, it is unclear to what extent their positive effects can be generalized to regular clinical practice. Treatment effects may be more modest outside RCTs because of different circumstances [25-27]. The second aim will be to assess the added value of therapist telephone availability outside office hours in case of crisis (TTA) during the 1.5 yrs of ST. The third aim will be to assess the problems that may arise during the implementation process.

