#### Assessments

Data are collected at four points in time: at baseline (T0), after 6 months of treatment (T1), 12 months of treatment (T2) eighteen months of treatment (T3) and a three- year follow-up (T4). Experienced research assistants with higher vocational training in psychology will be trained on the different sites in assessing patients for treatment outcome measures. Study researchers, screeners, research assistants and therapists are masked to treatment allocation during the screening period and the first assessment.

Table 1 summarizes the measures that are used at each point.

**Table 1 T1:** Summary of measures

**Measure**	**Baseline**	**6 months**	**12 months**	**18 months**	**Follow-up 36 months**

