### Outcome measures

#### Primary outcome measure

The primary outcome measure is the score on the BPDSI-IV, a DSM-IV BPD criteria- based semi- structured interview: this 70- item index represents the current severity and frequency of the DSM-IV BPD manifestations. This instrument shows excellent psychometric features (Cronbach's alpha = 0.85, interrater reliability, 0.99; validity and sensitivity to change [30,31]. Previous research [30,31] found a cut-off score [35] of 15 between patients with BPD and controls, with a specificity of 0.97 and a sensitivity of 1.00.

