#### Economic evaluation

In addition to the clinical evaluation, an economic evaluation will be performed to assess the cost-effectiveness of ST with versus ST without extra phone support outside office hours. In the cost-effectiveness analysis of ST with versus ST without phone support, the difference in costs will be related to the difference in effectiveness, resulting in an Incremental Cost Effectiveness Ratio (ICER). The cost-effectiveness analysis will be based on two different effectiveness outcomes. First, cost-effectiveness will be based on the proportion of patients recovered according to the BPDSI-IV, this reflecting the investment needed to cure one patient. Secondly, cost-effectiveness will be based on Quality Adjusted Life Years (QALY), which are calculated with the EQ-5D utility scores, resulting in costs per QALY. The cost-effectiveness analysis will be based on the principles of a societal perspective using a time horizon of 18 months. Costs will be monitored by means of a cost-interview that will take place during the patient interview alongside the other measurements. The cost-interview contains items about paid and unpaid work, study, daily activities, family burden, paid help, use of healthcare and social services, use of medication, consumption of alcohol and drugs and out-of-pocket expenses. Also the number of face-to-face and telephone contacts with the study therapists will be registered.

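### Masking of the BPDSI-IV assessors is given up after baseline on a general ground that does not fit a comparison of two arms receiving the same therapy

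*Protocol article*

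**What the plan says.** All references are to the protocol article.

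- **Primary outcome measure:** "The primary outcome measure is the score on the BPDSI-IV, a DSM-IV BPD criteria- based semi- structured interview". The recovery criterion, the reliable-change criterion and the recovery-based cost-effectiveness ratio are all derived from this score.
- **Assessments:** trained research assistants collect the outcome data. "Study researchers, screeners, research assistants and therapists are masked to treatment allocation during the screening period and the first assessment". Nothing is planned for the assessments at 6, 12, 18 and 36 months.
- **Strengths and limitations:** the assessments after baseline are done by "research assistants who cannot remain blinded to the treatment condition of the included patients, as is always the case in trials" of psychotherapy. The section adds that patients are not blind either, and offers self-report questionnaires as an offset.
- **Background:** the two modalities are "one with extra crisis support by the therapist outside office hours and one without such telephone support". Both are schema therapy.
- **Randomization:** the condition is allocated to therapists within centre, and each therapist treats two patients under that condition.
- **Treatment Adherence:** audiotapes are rated by independent raters who are masked to condition and outcome.
- **Economic evaluation:** costs are collected in "a cost-interview that will take place during the patient interview alongside the other measurements".

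**The concern.** In a psychotherapy trial, patients and therapists necessarily know what is being delivered. A separate outcome assessor does not have to. The protocol extends to the assessor a reason that holds for the other two, and so fixes unmasked scoring of the primary outcome at every post-baseline visit without a reason specific to this trial.

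What is at stake is the comparison of schema therapy with and without phone support. A semi-structured interview leaves room for judgement, and an assistant who knows the arm and has a view on phone support may score accordingly. The direction cannot be predicted. The Background reports that phone access was controversial in a pilot study and in mental healthcare generally, so expectations for or against it are both plausible. A lean in favour could create an apparent benefit, and a lean against could hide a real one. High interrater reliability (0.99 is cited) does not protect against this, because raters who share a lean still agree with each other.

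**Working it through.** The protocol gives no figure on this point, so the check is mainly a comparison of texts, followed by an illustration of size.

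**1. Does the stated reason fit the comparison?** The reason given is that assessors in psychotherapy trials never stay blind. Three parts of the protocol weigh against applying it here.
- Both arms receive the same therapy with the same session schedule and differ only in out-of-hours phone access. An assessor would not infer the arm from the type of treatment.
- The assistants are masked through screening and the first assessment, so masking them is already part of the procedures.
- Raters masked to condition are used for the adherence tapes.

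**2. How would an assistant learn the arm?**
- *Patient disclosure:* patients know their arm and are interviewed at four visits after baseline.
- *Knowing the therapist:* allocation is by therapist, so an assistant who knows a therapist's condition knows the arm of that therapist's patients.
- *Cost interview:* it takes place in the same patient interview and covers use of healthcare, which might bring up phone contacts. This is an inference, because contacts with the study therapist are not among the listed items.

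**3. Do the self-report measures repair the problem?** They are secondary outcomes, and they are completed by patients who know their arm. They avoid the assistant's influence but not the effect of knowing the condition, and they do not change the primary score.

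**4. Illustration of size.** Inputs from the Sample size section: 60 patients in total, taken as 30 per arm, and two-sided alpha 0.05. Assumed: no true effect, and a rating shift of b standard deviations between arms. Normal approximation, without baseline adjustment or therapist clustering:

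- SE of the standardized difference = √(2/30) = 0.258.
- P(reject) = Φ(b/SE − 1.96) + Φ(−b/SE − 1.96).

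| Assumed shift b | b/SE | P(reject) |
|---|---|---|
| 0 | 0 | 5.0% |
| 0.1 SD | 0.387 | 6.7% |
| 0.2 SD | 0.775 | 12.1% |
| 0.3 SD | 1.162 | 21.3% |

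The same formula covers the opposite lean. If the true effect is the planned 0.5 SD and the lean is 0.2 SD against phone support, the expected difference is 0.5 − 0.2 = 0.3 SD. The chance of a significant result then falls from about 49% (b = 0.5) to about 21%. The 49% does not match the power of 84 stated in the protocol. That is a separate question and does not bear on masking.

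**5. Why the size stays in SD units.** Conversion to BPDSI-IV points needs an SD that the protocol does not give. Working back from the reliable-change value of 11.70 requires a choice of reliability, since SD = 11.70 / (1.96 × √2 × √(1 − r)). With r = 0.85 (the cited alpha) this gives 10.9. With r = 0.99 (the cited interrater value) it gives about 42. The protocol does not say which reliability produced 11.70.

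**The case against.** The strongest case for the protocol is that masking would be fragile and that the authors are open about the limitation. Patients know their arm and talk to the assistant repeatedly. The arm is fixed by therapist, the assistants are trained on the sites, and the experiences of therapists and assistants are discussed in project and supervision meetings. Some assistants would be unblinded whatever was done. This stands as a limit on what the fix can achieve. It is not a reason to plan no masking at all, and disclosing a risk does not reduce it.

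A reader might go further and infer that the protocol builds in its own unblinding by having the assistant ask patients how often they phoned their therapist. The documents do not support this. The Economic evaluation section says "Also the number of face-to-face and telephone contacts with the study therapists will be registered" but names no source and does not list it as a cost-interview item. The sections on registration of phone contacts and of therapy sessions assign these records to therapists. The same-session cost interview is therefore one possible clue, and patient disclosure and knowledge of the therapist are better supported.

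It is also fair to say that the protocol has another main aim. The comparison of pre-post change with the earlier randomized trial is not affected in the same way by a lean that depends on arm.

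**Conclusion.** The point holds as a matter of design choice. The protocol gives up assessor masking on a blanket ground that does not fit two arms receiving the same therapy, and the offset it offers does not remove the resulting risk to the phone-support comparison on the primary outcome.

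The size is illustrative only. It rests on assumed shifts of 0.1 to 0.3 SD, 30 patients per arm and a simple two-group test. Nothing in the documents shows that a lean exists, how large it would be or which way it would go. The conclusion does not depend on a particular value, because the remedy is cheap. It also does not amount to saying that full blinding can be achieved.

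**What to change.** 1. State that research assistants are intended to stay masked at all assessments. Withhold the therapist allocation and, as far as possible, the therapist's identity from them.
2. Have the BPDSI-IV scored and locked before the cost interview starts.
3. Take contact counts only from the therapist forms. The phone-contact form is described only for therapists in the phone-support arm, so if telephone contacts are to be counted in both arms, therapists in the other arm need to record them as well.
4. Ask patients before each interview not to mention phone access.
5. Have the assistant record a guess of the condition after each BPDSI-IV, and report the guesses by arm.
6. In Strengths and limitations, delete the clause saying that assessors are always unblinded in such trials. Describe instead the masking attempted and the unblinding that remains.

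The cost is a small change to the visit order and one extra form item, with no extra staff. Some assistants will still learn the condition, and the recorded guesses will help show how often.

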### Timeframe of the study

In December 2005 the randomized treatment study has been started up.

Month 1-6: Recruitment of departments, therapists and research assistants.

Month 6-8: Training of therapists and research-assistants.

Month 9-21: Screening and inclusion of borderline patients at the different locations. Start of the data collection for the treatment study. Supervision of the treatments. Start of data entry and purging of databases.

Month 27-43: Completion of data collection. Completion of purging and analysis of the data. Publication on the short-term findings.

Month 43 until 2010 Three-year follow-up assessments. Publication on the (cost-)effectiveness of ST. Dissemination of the results (e.g. presentation of study results at national and international conferences). Working on the implementation of ST in the Netherlands.

### Description of risks

There are no specific risks related to this study.
